## Abstract

**Background:**

The prolonged air leak is probably the most common complication following lung resections. Around 10–20% of the patients who undergo a lung resection will eventually develop a prolonged air leak. The definition of a prolonged air leak varies between an air leak, which is evident after the fifth, seventh or even tenth postoperative day to every air leak that prolongs the hospital stay. However, the postoperative hospital stay following a thoracoscopic lobectomy can be as short as 2 days, making the above definitions sound outdated. The treatment of these air leaks is also very versatile. One of the broadly accepted treatment options is the autologous blood pleurodesis or “blood patch”. The purpose of this trial is to investigate the impact of a prophylactic autologous blood pleurodesis on reducing the duration of the postoperative air leak and therefore prevent the air leak from becoming prolonged.

**Methods:**

Patients undergoing an elective thoracoscopic anatomic lung resection for primary lung cancer or metastatic disease will be eligible for recruitment. Patients with an air leak of > 100 ml/min within 6 h prior to the morning round on the second postoperative day will be eligible for inclusion in the study and randomization. Patients will be randomized to either blood pleurodesis or watchful waiting. The primary endpoint is the time to drain removal measured in full days. The trial ends on the seventh postoperative day.

**Discussion:**

The early autologous blood pleurodesis could lead to a faster cessation of the air leak and therefore to a faster removal of the drain. A faster removal of the drain would relieve the patient from all the well-known drain-associated complications (longer hospital stay, stronger postoperative pain, risk of drain-associated infection, etc.). From the economical point of view, faster drain removal would reduce the hospital costs as well as the costs associated with the care of a patient with a chest drain in an outpatient setting.

**Trial registration:**

German Clinical Trials Register (DRKS) DRKS00030810. 27 December 2022

## Introduction

### Background and rationale {6a}

Every year, around 1.8 million people are diagnosed and 1.6 million die of lung cancer [1]. The morbidity associated with the disease is horrifying. In 2016, lung cancer was responsible for 36.4 million disability-adjusted life years (DALYs) [1]. The NLST trial showed a significant reduction in the mortality of lung cancer after routine screening with a low-dose CT scan of the chest [2]. However, the screening has not been broadly implemented yet, expecting that the rate of patients being diagnosed with early-stage lung cancer will substantially increase in the following years.

The most common complication following lung surgery is postoperative air leak. Air leaks result from incomplete closure of small airways during the division of lung tissue and can be monitored through the chest drain, which is placed at the end of an operation. Most air leaks heal within the first 24 h after a lung procedure. However, 10–20% of the operated patients will eventually develop a prolonged air leak [3].

The exact incidence of postoperative air leak widely varies, mainly due to the absence of a commonly accepted definition. The traditional definition of a prolonged air leak is an air leak, which lasts over 7 days. This definition is based on studies using analogue drain systems (underwater seal) to monitor the air leak. The expansion of video-assisted thoracoscopic surgery, the modern anaesthetic techniques and the evolution brought by the implementation of the ERAS pathway [4] have reduced the postoperative hospital stay after a lobectomy down to 2–3 days, making the definition of prolonged air leak clearly outdated. Furthermore, the modern electronic suction devices, which are nowadays used to monitor the air leak, enable a much more objective quantification of the air leak. It is therefore reasonable to expect that postoperative air leaks will soon become the most relevant complication in thoracic surgery.

The purpose of this trial is to investigate the impact of a prophylactic autologous blood pleurodesis in reducing the duration of the postoperative air leak and therefore the time till the drain can be removed.

### Objectives {7}

The hypothesis of the trial is that autologous blood pleurodesis will lead to a faster cessation of the air leak and prevent the air leak from becoming prolonged. This should lead to a shorter time that the drain needs to be kept in situ and therefore reduce the hospital stay, the drain-associated burden for the patient and the treatment costs.

### Trial design {8}

The ERASURE trial is an investigator-initiated, multicentre, prospective, randomized (1:1), controlled, open-label, parallel-group trial.

### Eligibility criteria {10}

#### Key inclusion criteria

Adult patients undergoing a scheduled thoracoscopic (video-assisted thoracoscopic surgery (VATS)) anatomic lung resection for primary or secondary lung tumours and presenting with an air leak > 100 ml/min within 6 h prior to the morning round of the second postoperative day will be eligible for enrollment.

#### Key exclusion criteria

The following are the key exclusion criteria:Patients undergoing an open lobectomyPatients undergoing complex lobectomies (bronchoplastic reconstructions, etc.)Patients requiring invasive or positive pressure non-invasive ventilation except in the first 6 h following the operationPatients undergoing re-operation during the same hospital admissionSuspected or proven bronchial stump leakageIntraoperative use of sealants, pleural tents or talcum

All trial interventions will be performed either by surgeons or by surgical trainees.

### Who will take informed consent? {26a}

Informed consent will be obtained by the investigator (local principal investigator-consultant surgeon) or a person designated by the investigator in accordance with the current Good Clinical Practice Guideline and the Declaration of Helsinki. Prior to the beginning of the recruitment, each participating centre and coordinating investigator will be responsible for obtaining local institutional review board (IRB)/IEC approval of the written informed consent, study protocol and any other written information that will be provided to subjects.

### Additional consent provisions for collection and use of participant data and biological specimens {26b}

Participant data will be handled in accordance with the current Good Clinical Practice Guideline and the Declaration of Helsinki. No biological specimens will be obtained in this trial.

### Interventions

#### Explanation for the choice of comparators {6b}

Patients who enter the control group will be treated conservatively. The electronic suction device will be set on gravity mode (− 8 cmH_2_O or − 0.8 kPa). No interventions are allowed in order to speed up the healing of the air leak. This is the routine way to deal with postoperative air leaks in most thoracic centres worldwide. After the seventh postoperative day, patients with persisting air leak will be treated according to each participating centre’s preference. In case the air leak stops before the seventh postoperative day, the drain will be removed accordingly.

#### Intervention description {11a}

Patients who meet the eligibility criteria will be randomized. Patients who enter the interventional group will receive an autologous blood pleurodesis. A sterile bedside set-up will be created for the procedure. A leur-lock connector will be attached to the chest drain in a sterile manner; 100–120 ml of patient blood will be obtained from a peripheral or central venous line. The blood will be then administered through the leur lock connector into the chest drain. The chest drain will be then flushed with 20 ml of sterile normal saline to avoid clotting of the drain. The tubing of the electronic suction system will be then raised 60 cm above the level of the patient. The patient will be asked to change places and move while in bed in order for the blood to spread equally in the pleural cavity. After the 2 h, the patient will be free to mobilize and the electronic suction system will be turned on and set on gravity mode (− 8 cmH_2_O or − 0.8 kPa). In case the air leak persists, the procedure will be repeated on the third postoperative day. After that, no further interventions are scheduled till the seventh postoperative day. After the seventh postoperative day, patients with persisting air leak will be treated according to each participating centre’s preference. In case the air leak stops before the seventh postoperative day, the drain will be removed accordingly (regardless of the amount of fluid drained).

#### Criteria for discontinuing or modifying allocated interventions {11b}

Any modifications that need to be applied on the chest drain (e.g. patient’s condition requires change in the suction or other intervention) will be considered interventions and documented on the electronic case report form. Cross-over is not permitted before the seventh postoperative day, when the formal trial participation ends. After the seventh postoperative day, any type of treatment is permitted, as it is no longer associated with the trial.

#### Strategies to improve adherence to interventions {11c}

In order to improve adherence to the intervention protocol, we have created a standard operating operating procedure (SOP) for the autologous blood pleurodesis.

#### Relevant concomitant care permitted or prohibited during the trial {11d}

No changes to the drain suction, manipulations on the drain (e.g. pulling back the drain) or any other ways to influence an air leak are permitted during the trial.

#### Provisions for post-trial care {30}

Not applicable. Autologous blood pleurodesis is a well-established method for treating postoperative air leaks with a very low rate of adverse events. Patients developing complications following autologous blood pleurodesis will be treated according to the local investigators’ preference. No compensation will be provided.

### Outcomes {12}

#### Primary endpoint

Time to drain removal measured in full days

#### Secondary endpoints

The following are the secondary endpoints:Time to cessation of the air leak (calculated in postoperative hours)Length of postoperative stay measured in full daysRate of (redo) interventions due to persistent air leaksRate of pleural empyemas

#### Outcome measures

Time to drain removal measured in full days was chosen as the primary endpoint for several reasons:

(1) The intervention of this trial is a locally applied therapy enabling a more effective and faster sealing of the postoperative air leak. The efficacy of this treatment is more accurately evaluated by the time to drain removal. (2) It reflects the success or failure of the treatment directly, since removing the drain implies the cessation of the postoperative air leak. (3) It is a parameter, which is unique and irreversible throughout the patients’ treatment and therefore not susceptible to interpretation bias from the medical team. (4) The parameter is clinically relevant and practical to use. The main reason is that chest drains are not usually removed overnight. Likewise, patients are usually not discharged overnight. (5) Several studies have analysed the efficacy of autologous blood pleurodesis using the time to drain removal as the primary efficacy endpoint making it a widely accepted parameter to use as a primary outcome measure [5, 6]. The secondary outcomes include all relevant perioperative and patient-reported outcomes in thoracic surgery trials using widely accepted definitions. In order to assess the variability of the drain removal protocols among the participating centres, the shortest potential drainage time in postoperative hours will be calculated by retrieving the relevant data from the electronic suction device memory. Furthermore, in order to assess further complications associated with the procedure and potentially with the intervention (using the Clavien-Dindo grading system [7], the length of the postoperative stay calculated in full days will be evaluated. The rate of re-interventions due to persistent air leak after the initial removal of the drain will be also measured in order to detect treatment failures. The pleural empyema is the only well-documented complication of autologous blood pleurodesis with an incidence of 1.5% [8].

### Participant timeline {13}

Screening for eligibility will take place in the outpatient clinic (Fig. 1 and Table 1). Patients will be consented for the trial. Patients who undergo a thoracoscopic, anatomic lung resection and still have an air leak > 100 ml/min within 6 h before the morning ward round on the second postoperative day will be randomized.

**Fig. 1 Fig1:**
[figure not shown]
Trial flowchart

**Table 1 Tab1:** Trial timeline

	Baseline	Randomization	Follow-up				
	Visit 1	Visit 2	Visit 3	Visit 4	Visit 5	Visit 6	Visit 7
	OPC	POD 2	POD 3	POD 4	POD 5	POD 6	POD 7
Baseline data	x	x					
Informed consent	x						
Eligibility	x	x					
Intraoperative data		x					
Intervention		x/0	x/0				
Clinical events, complications		x	x	x	x	x	x
SAE		x	x	x	x	x	x

*OPC* outpatient clinic, *POD* postoperative day, *SAE*: serious adverse events, *x* shows when a specific step of the trial will take place, *x/0* shows if the intervention will be performed depending on the trial group

Patients who are randomized in the intervention group will receive an autologous blood pleurodesis on the same day and if the air leak does not resolve, on the third postoperative day. After that, no further interventions are permitted unless the clinical condition of the patient requires deviation from the trial. Patients who are randomized in the control group will be treated according to the watchful waiting strategy until the seventh postoperative day. Trial participation ends on the seventh postoperative day, and every patient can be treated according to the preferences of the participating centre.

### Recruitment {15}

Anatomic lung resections belong to the most commonly performed thoracic procedures. The incidence of the prolonged air leak using the period of 7 days to define ‘prolonged’ is 10–20% [3]. Other studies report even higher incidence than that. These data are based on older studies, where the air leak was measured with the traditional underwater seal systems. The new electronic suction devices, which will be used in this trial, are far more sensitive in identifying and quantifying air leaks than the traditional underwater seal. This study will assess the role of autologous blood pleurodesis as a prophylactic treatment by applying autologous blood pleurodesis on the second and third postoperative days. It is therefore rather conservative to assume that 20% of the screened patients will have an air leak > 100 ml/min on the first postoperative day. This will result in 710 patients needing to be screened for this trial. This trial will be performed among seven high-volume institutions. At each institution over 200 patients are treated for primary lung cancer every year. This translates into approximately *n* = 1500 patients that will be screened during the enrolment period of 12 months. After the exclusion of patients not meeting the eligibility criteria and those declining participation in the study, a sufficient number of patients will remain eligible for inclusion. In fact, just two patients need to be enrolled per centre every month to meet the anticipated enrolment period, which appears feasible. Furthermore, all centres are academic institutions with a dedicated trial centre ensuring the screening of all scheduled patients and inclusion of all eligible patients.

### Assignment of interventions: allocation

#### Sequence generation {16a}

Computer-generated allocation, no stratification planned. All trial patients will be randomized after confirmation of eligibility on the second postoperative day.

#### Concealment mechanism {16b}

The randomization process is implemented in the electronic case report form, and the sequence is only generated after the investigator has confirmed the eligible for every included patient.

#### Implementation {16c}

A computerized tool that is embedded in the electronic case report form will generate the randomization sequence (1:1 randomization).

### Assignment of interventions: blinding

#### Who will be blinded {17a}

Open-label trial, no blinding.

#### Procedure for unblinding if needed {17b}

Not applicable.

### Data collection and management

#### Plans for assessment and collection of outcomes {18a}

Patient data will be assessed and collected by the local surgical team and will be entered in the electronic case report form. Responsible for the data accuracy is the local primary investigator. The electronic case report form is designed to request an electronic signature from the investigator after having entered any type of data. The pseudonymization of the data will be performed locally at each participating centre. Each centre will have full access to its own data. The principal investigator and the co-investigator will have full access to the complete pseudonymized dataset. A summary of the data management and confidentiality has been included both in the trial protocol and in the consent form that will be handed over to the study participants. Training of the investigators is scheduled before the beginning of the trial in order to ensure correct data entry.

#### Plans to promote participant retention and complete follow-up {18b}

The participation in this trial and all associated interventions and data acquisition are completed during the hospital stay of the patients. A high adhesion to the trial interventions and low rate of “loss to follow-up” are to be expected.

#### Data management {19}

Data will be entered electronically in the electronic case report form (eCRF) The electronic case report form is an online platform, which has been specifically set up by the Interdisciplinary Center for Clinical Trials (IZKS Mainz) for the purpose of this specific trial. An electronic signature request has been embedded in several levels of the eCRF and is required in order to proceed throughout the eCRF. Errors will be detected by programmes, which are designed to detect missing data or deviations from the expected outcomes/values. The process of data extraction, analysis and dissemination will only include pseudonymized data. The Interdisciplinary Center for Clinical Trials (IZKS Mainz) will be responsible for data management and data archive. Data will be stored in a pseuodonymized form for 25 years. All data specified in the trial protocol will be documented in a clinical database. The investigator or the designated representatives are obliged to clarify and solve queries. If no further corrections are to be made in the database, it will be locked and used for statistical analysis.

#### Confidentiality {27}

Electronic data will be kept confidential and not accessible to any unrelated person or third party throughout the whole trial. The pseudonymization process will be performed locally at each participating centre. The coordinating investigator of each participating centre will be responsible for the confidentiality of the pseudonymization and the adherence to the Good Clinical Practice guidelines.

All data management procedures at the coordinating centre will be conducted according to written defined standard operating procedures (SOPs) of the IZKS that guarantee an efficient conduct complying with Good Clinical Practice (GCP) and under strict observance of national and EU regulations. Source data are to be stored for at least 10 years after trial termination in the centre archive. At the end of the study, the data will be transformed into different data formats for archiving to ensure that it can be reused.

##### Dissemination of results

The trial has been registered at the German Clinical Trials Registry (DRKS) and the trial protocol will be published. International guidelines such as SPIRIT and CONSORT will be strictly adhered to. Results will be presented at national and international conferences. Publication in international peer-reviewed journals is intended.

#### Plans for collection, laboratory evaluation and storage of biological specimens for genetic or molecular analysis in this trial/future use {33}

N/A, no biological specimens will be collected as part of this trial.

## Statistical methods

### Statistical methods for primary and secondary outcomes {20a}

The primary endpoint (the time to drain removal in full days) will be analysed within a Cox regression model with treatment as a fixed factor and centre as a covariate. Model assumptions will be checked by Schoenfeld residuals. The two-sided significance level is set to *α* = 5%. The primary analysis population is the ITT population consisting of all randomized patients. Treatment differences will be displayed by the estimate of the hazard ratio and the 95% confidence interval. Sensitivity analyses will be done by adding additional variables like smoking (yes/no) and sex in the regression model, although sex is not known as an influencing factor for time to drain removal.

Safety: Absolute and relative frequencies of adverse events.

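### The primary Cox model leaves out the day-2 air-leak rate, a pre-randomisation reading available for every randomised patient; this forgoes efficiency but is not a sample-size error

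*Protocol article*

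**What the plan says.** The section on statistical methods for primary and secondary outcomes {20a} fixes the primary model: time to drain removal in full days is to be "analysed within a Cox regression model with treatment as a fixed factor and centre as a covariate". It goes on: "Sensitivity analyses will be done by adding additional variables like smoking (yes/no) and sex in the regression model", and then adds "although sex is not known as an influencing factor for time to drain removal". Leak rate appears in none of these models, and Sequence generation {16a} plans no stratification.

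The leak is nevertheless measured in every patient before allocation. The key inclusion criteria call for patients "presenting with an air leak > 100 ml/min within 6 h prior to the morning round of the second postoperative day", and Participant timeline {13} says that those who "still have an air leak > 100 ml/min within 6 h before the morning ward round on the second postoperative day will be randomized". Neither the inclusion nor the exclusion criteria set an upper limit on the rate.

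On the quality of the reading, Background and rationale {6a} says that electronic suction devices "enable a much more objective quantification of the air leak". Recruitment {15} says that the devices to be used in this trial "are far more sensitive in identifying and quantifying air leaks than the traditional underwater seal". On the link to the endpoint, Outcome measures justifies drain removal as the primary outcome partly "since removing the drain implies the cessation of the postoperative air leak".

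**The concern.** The leak rate at entry is the baseline value of the process that decides when the drain is removed. A patient just above 100 ml/min and one far above it are likely to have different prospects of drain removal by POD 7, whichever arm they are in. The primary model treats them as exchangeable within centre.

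Leaving a prognostic covariate out of a Cox model has two consequences. The treatment hazard ratio (HR) is pulled towards 1 relative to the effect at a given leak rate, and power falls relative to the adjusted model. Also, with no stratification, any chance difference in leak size between the arms goes uncorrected in the primary estimate. Adjusting for it only after the data are seen would be open to challenge.

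**Working it through.** **Inputs from Sample size {14}.** Medians of 4 and 2 days, 7 days of observation with no accrual time, two-sided 5%, 90% power, log-rank test, N = 110, with 120 randomised.

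**Step 1: reproduce the stated N.** Under exponential times the HR is 4/2 = 2 for removal.

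- Events (Schoenfeld, 1:1): 4 × (1.960 + 1.282)² / (ln 2)² = 4 × 10.51 / 0.480 = 87.5, so 88.
- Removal by day 7: control 1 − 2^(−7/4) = 0.703; experimental 1 − 2^(−7/2) = 0.912; mean 0.807.
- N = 88 / 0.807 = 109.0, which becomes 110 in two equal arms. Power at 110 is 90.4%.

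The stated figure reproduces, and no covariate entered it.

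**Step 2: power without and with leak rate.** The protocol does not say how strongly leak rate predicts removal, so the strength is an assumption and is varied, starting from zero. The simulation used N = 110, exponential times given leak, conditional HR 2, control-arm median 4 days, standardised normal log leak, times rounded up to full days, censoring at day 7, and Cox models with Efron ties. There were 2 × 2000 runs per row. Centre was not simulated.

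| Log-hazard per SD of log leak (assumed) | Power without leak | Power with leak | Mean HR without leak | Mean HR with leak |
|---|---|---|---|---|
| 0 | 90% | 90% | 1.99–2.01 | 2.00–2.02 |
| 0.25 | 88% | 90% | 1.96–1.97 | 2.02–2.03 |
| 0.5 | 80% | 89% | 1.82–1.86 | 1.99–2.01 |
| 0.75 | 71% | 86% | 1.74 | 1.99–2.00 |
| 1.0 | 58% | 83% | 1.62–1.63 | 1.95 |

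The cost of the omission is the gap within a row: 0, 2, 9, 15 and 25 points. A second simulation over 7 days agreed: 80% against 89% at 0.5, and 70% against 87% at 0.7. Adding a non-prognostic binary factor such as sex in place of leak changed power by less than 1 point.

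**Step 3: the observation window.** From randomisation on POD 2 to POD 7 is five days. With a 5-day window the mean removal probability is 0.701, which gives 110 × 0.701 = 77 events and about 86% power before any covariate is considered. Simulated power without and with leak is then 81% and 86% at 0.35, 77% and 84% at 0.50, and 67% and 82% at 0.70. The gaps are 5, 7 and 15 points. Only these gaps bear on the present point; part of the drop below 90% comes from the shorter window.

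**Step 4: chance imbalance.** With 60 per arm, the standard error of the between-arm difference in standardised log leak is √(2/60) = 0.18, so 95% of differences lie within about ±0.36 SD. At an assumed 0.5 per SD, a difference of 0.36 shifts the log-HR by 0.5 × 0.36 = 0.18, a factor of exp(0.18) = 1.2.

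**The case against.** Treatment plus centre is a valid model, and the promised power never relied on adjustment. A reader might infer from the table that the trial is underpowered as planned. The documents do not support that. The sample size reproduces, and its calculation works with group-level exponential curves, for which HR 2 is naturally a marginal effect. On that reading the 90% stands. A marginal HR nearer 1 than the conditional one is a different estimand, not bias.

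A reader might also infer that sex has been put in the place of leak rate at a cost in power. That goes too far. Smoking is named first, the wording leaves the list open, so leak could still be added as a sensitivity analysis, and neither variable enters the primary model.

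The size of the loss is assumed. Nothing in the documents rules out a weak predictor, with a loss of 0 to 2 points. Very large leaks may also be rarer than the open upper limit suggests, because suspected stump leakage and re-operation are exclusions. Randomisation already protects the type I error against chance imbalance, and the open-label design has no bearing on a reading taken before allocation.

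Two practical objections stand in full. Eligibility refers to a 6 h window, not to one value, so a reading has to be chosen. And section {20c} rules out imputation, so a missing reading would drop a randomised patient from the primary model.

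What these objections leave intact is that the primary model is fixed without a baseline value already read for entry. An open sensitivity list does not repair the primary analysis.

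**Conclusion.** The point holds as forgone efficiency in a pre-specified primary analysis, and it should be corrected. It is neither a contradiction nor an error in the stated sample size. The direction is secure if leak rate is prognostic, which the protocol's own link between leak cessation and drain removal makes likely. The size is not secure: with a conditional HR of 2 and 7 days, the loss is nil for a non-prognostic leak, about 2 points at 0.25 per SD, 9 at 0.5 and 15 at 0.75. If HR 2 is marginal, the planned 90% is kept and the loss is only a gain not taken. In the no-effect row, adding the covariate left power at 90%, so adjusting for it carries a negligible penalty.

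**What to change.** - Add log(air-leak rate in ml/min) as a continuous covariate to the primary Cox model, with treatment and centre.
- Define which reading in the 6 h eligibility window is used, for example the last one before randomisation.
- Make that value a mandatory eCRF field at randomisation, so that no randomised patient drops out of the model. Randomisation already runs inside the eCRF after eligibility is confirmed; whether the form already stores the value cannot be seen from the article.
- Report the model without leak rate as a sensitivity analysis, and state that the primary HR is conditional on leak rate.

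The cost is one model term, one data field, and a treatment HR that must be read as conditional on leak rate. No extra measurement is needed, and sample size and patient care do not change. The change should be made before anyone sees outcome data by arm.
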